**STUDY PROTOCOL – TAPE TRIAL**

**Study design and ethical considerations**

A cross-over, longitudinal, clinical trial with three intervention arms will be conducted in the Sports Performance Laboratory of the European University of Madrid (Spain), adhering to the Helsinki Declaration. Each participant will complete and signed a written consent form before being enrolled in the study.

**Sample size calculation**

The sample size will be calculated using the G*Power 3.1.9.2 software (G*Power©, University of Dusseldorf, Germany). This analysis will employ a two-tailed hypothesis, an alpha error probability of 0.05, and a beta error of 0.2. A pilot study involving 10 participants will analyze the partial eta squared effect size for the primary outcome, which was the height in the SLDJ between groups and time.

**Participants**

The inclusion criteria will be (1) males and females (2) between 18 – 45 years old (3) well-trained, with a weekly training schedule of at least two days and a total of 20 km of running. The exclusion criteria will be determined by the presence of musculoskeletal lower limb or lumbopelvic pathology in the last year.

**Randomization**

The randomization of the participants will be carried out with the random function of Microsoft Office Excel (Microsoft Corporation, Redmond,WA, USA).

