**Intervention protocol**

Voluntary participants will be assessed for eligibility, collection of demographic data, and completion of a maximal effort 5-minute run test on a 400-m track to determine their individual maximal aerobic speed.

Subsequently, participants will be scheduled for three sessions (once a week) to undergo the intervention under three different conditions, with the order randomized: one without a bandage (CONTROL), one with a tape bandage, and another with KT.

The bandaging will be consistently applied to the dominant leg by a physiotherapist with ten years of clinical experience specializing in ankle and foot injuries in runners, within the Sports Performance Laboratory of the European University of Madrid.

A 10-minute warm-up will be performed based on lower limb mobility exercises, ballistic stretching and running. Subsequently, an assessment of lower limb stability, ankle dorsiflexion mobility, electromyographic activation of the ankle muscles, and jumping ability will be performed, before starting the treadmill protocol.

Following this evaluation, a fatigue protocol will be implemented, involving a 30-minute run at 85% of the maximal aerobic speed on a treadmill. Once completed, an immediate reevaluation will be conducted for all previously administered tests, to collect the same variables as at the beginning of the running protocol.

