**Statistical analysis**

The statistical analysis will be performed with the SPPS software version 29 for Windows. First, data distribution will be assessed with the Shapiro-Wilk test or Kolmogorov-Smirnov test. Then, a one-way ANOVA will be performed to analyze the difference between groups at baseline. Finally, a two-way ANOVA of repeated measures (3 x 2; 3 groups and 2 times of measurement) will be carried out to analyze the difference between groups pre and post treadmill protocol. The investigator who performs the statistical analysis will be blinded. All variables will be analyzed individually, and multiple comparisons will account for using a Bonferroni correction. The significance level will be set at 0.05.

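### Balance of the six condition orders over the weekly sessions is not stated, and the fixed 3 x 2 ANOVA has no session term: a cost in chance imbalance and precision, not systematic bias

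*Protocol*

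**What the plan says.** The protocol's design section describes the study thus: "A cross-over, longitudinal, clinical trial with three intervention arms will be conducted". Under Intervention protocol, "participants will be scheduled for three sessions (once a week) to undergo the intervention under three different conditions, with the order randomized". All tests are done before the treadmill run, and afterwards "an immediate reevaluation will be conducted for all previously administered tests", so each session yields a pre and a post value.

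The Randomization section is one sentence: "The randomization of the participants will be carried out with the random function of Microsoft Office Excel". It names a tool. It mentions no blocks, no Latin square and no equal use of the six orders, and it does not say that the draw is free of such restrictions.

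The Statistical analysis section fixes the model: "a two-way ANOVA of repeated measures (3 x 2; 3 groups and 2 times of measurement) will be carried out". It also plans a separate comparison before the run: "a one-way ANOVA will be performed to analyze the difference between groups at baseline". Neither analysis has a factor for session, period or sequence.

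**The concern.** In a cross-over, each participant's condition effect is read from differences between sessions, so anything that changes from week to week enters those differences. Here a session trend is plausible on the protocol's own description. The single-leg drop jump (primary outcome) and the Y balance test are skill tasks done six times. The hard treadmill run is repeated weekly. The screening visit as described contains neither the jump nor the balance test. The maximal isometric contractions for EMG normalisation take place only on the first running day, so that session differs from the other two in any case.

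If one condition happens to fall later on average than another, part of any trend is credited to the bandage, and a model without session cannot separate the two. If the orders happen to be even, the trend still sits in the residual and weakens the test. Both costs grow with the trend and could be avoided at the design stage. The allocation cannot be repaired after enrolment.

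**Working it through.** **Inputs from the protocol:** three conditions, three weekly sessions, random order, pre and post values in each session, a 3 x 2 model, alpha 0.05. The protocol gives no sample size, SD or learning effect, so there is no stated figure to reproduce.

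**Assumptions:** N of 12 to 30; an additive trend b of 0 to 1.0 within-participant SD per session; a true effect of 0 or 0.8 SD in one condition; order drawn independently for each participant, or balanced over the six orders.

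**1. Chance imbalance under independent draws.** For two given conditions, the difference in session number within a participant is ±1 with probability 2/3 and ±2 with probability 1/3. Its mean is 0 and its variance is 1 × 2/3 + 4 × 1/3 = 2. The mean over N participants therefore has SD √(2/N):

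- N = 12: 0.41
- N = 20: 0.32
- N = 24: 0.29
- N = 30: 0.26

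At N = 20 the absolute gap has median 0.20 and 90th percentile 0.50. The accidental shift in the contrast is b times the gap. With b = 0.5 this is 0.5 × 0.20 = 0.10 SD at the median and 0.5 × 0.50 = 0.25 SD at the 90th percentile.

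**2. Expected bias and type I error.** The expected gap is zero, so the expected shift is zero. In simulation (2,000 null runs per setting) the mean shift was within 0.014 SD of zero throughout. Type I error without a session term was 0.043 to 0.059.

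**3. Precision of the condition main effect.** With balanced orders, the session values −b, 0, +b within a participant add (b² + 0 + b²)/2 = b² to a residual variance of 1. At b = 0.5 that is 25%. Simulation at N = 24 with a 0.8 SD effect (1,000 runs for power):

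| Trend per session | Order | Type I, no term | Type I, with term | Power, no term | Power, with term |
|---|---|---|---|---|---|
| 0 | independent | 0.050 | 0.052 | 0.79 | 0.77 |
| 0.25 SD | independent | 0.059 | 0.055 | 0.76 | 0.76 |
| 0.5 SD | independent | 0.043 | 0.042 | 0.72 | 0.79 |
| 1.0 SD | independent | 0.052 | 0.059 | 0.48 | 0.76 |
| 0 | balanced | 0.054 | 0.054 | 0.80 | 0.80 |
| 0.5 SD | balanced | 0.023 | 0.047 | 0.71 | 0.81 |
| 1.0 SD | balanced | 0.002 | 0.050 | 0.39 | 0.81 |

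A second run at 0.5 SD with independent draws gave 0.69 without the term and 0.77 with it, so about 0.70 against 0.77-0.79.

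**4. Which contrasts are exposed.** Let session s add δₛ to both the pre and the post value. Then (post + δₛ) − (pre + δₛ) = post − pre, and δₛ drops out of the condition-by-time interaction and of its residual. It stays in the condition main effect, in the baseline ANOVA and in any post-run comparison between conditions. The interaction is touched only if session changes the pre-to-post response itself, for example through habituation to the run.

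**The case against.** A reader might infer that learning across sessions biases the comparison of bandages. The protocol does not support that. Order is randomised, so a trend is tied to no condition. Over repeated allocations the expected bias is zero, and the ANOVA error term already allows for the chance variation. This objection stands. What it leaves is the imbalance in the one allocation that will be realised, and the lost power.

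A reader might also infer that the randomisation is unrestricted. The protocol is silent: Excel's random function can shuffle a balanced list as easily as it can draw an order for each participant, and the detail may be recorded elsewhere. So the point can only be that balance is not stated. The model, by contrast, is stated, and session is not in it.

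The strongest objection concerns the target. The primary outcome is framed across groups and time, and an additive session shift cancels in that interaction. This also stands, and it confines the figures above to the main effect and the single-time comparisons. It does not dispose of the point: the plan includes the baseline comparison between conditions, and a change in fatigue response over three identical runs is plausible, though its size cannot be derived from the protocol.

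Finally, the gain depends on the trend. With no trend the term costs about 0.02 in power, and at 0.25 SD per session it is neutral.

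**Conclusion.** The point holds as one of balance and efficiency. The protocol does not state that the six orders are balanced over sessions, and its fixed model omits session. A session trend would not bias the comparison systematically or inflate type I error. In a trial of about 20 participants it could move a given contrast by about 0.10 SD typically and 0.25 SD in the worst tenth of allocations, with a trend of 0.5 SD per session. With 24 participants and a 0.8 SD effect, the same trend would cost roughly 0.07 to 0.09 in power for the condition main effect (0.79 − 0.72 and, on average, 0.78 − 0.70 fall in this range). Sample size, effect and trend are all assumed. With little or no trend the loss vanishes. The condition-by-time interaction is affected only if session alters the pre-to-post change. This is a worthwhile, inexpensive improvement rather than a fatal flaw.

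**What to change.** 1. State that the six orders are allocated from a list generated beforehand in permuted blocks of six. Each complete block uses every order once, so a sample size that is a multiple of six gives exact balance over sessions. Excel can still do the shuffling.
2. Replace the 3 x 2 ANOVA with the corresponding linear mixed model: participant random; condition, time and condition-by-time fixed; and session number (1 to 3) as an added fixed effect. Include a random term for each participant's visit, so that the pre and post values of one session are not treated as independent. Add session-by-time if the interaction is to be protected too.
3. Put session into the baseline comparison between conditions in the same way.

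Adopt both the balanced list and the session term. Balanced orders alone remove the chance shift but make the main-effect test conservative: type I error is about 0.02 at 0.5 SD per session.

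The cost is 2 degrees of freedom per added term, about 0.02 in power if there is no trend and orders are drawn independently, a list prepared before enrolment, and a change of model procedure. No extra visits or measurements are needed.

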**Variables**

**Sociodemographic variables**

Athlete’s gender (male or female), age (years), height (cm), weight (kg), Body Mass Index (BMI) (kg/cm2), dominant limb (right or left), and history of ankle sprains will be collected as descriptive data. In addition, the following weekly training characteristics will be collected: number of training days, running distance (km), average pace (min/km), presence of specific lower limb and core muscle strength, or proprioceptive training.

**Lower limb stability:** The Y balance test will be used to analyze the stability of the dominant lower limb. Participants will stand in the center of the Y-shaped area. While balancing on one leg, they will have to reach as far as possible with the other limb without falling along each of the three branches of the Y: anterior, posterior-right and posterior-left. Measurements will be taken from the tip of the foot in each direction, with three trials conducted to obtain an average.

**Ankle dorsiflexion mobility** will be measured through the MyROM app during the Lunge test. In a knight's stance, with the dominant limb on the ground and hands on the waist, participants will be instructed to lean forward as far as possible without taking off the heel. A mobile phone will be placed along the tibia to track the dorsiflexion angle, and measurements will be recorded on the screen. Each participant will undergo three measurements and the mean between measurements will be calculated.

**Electromyographic activation of the ankle muscles** will be measured during the SLDJ, in the following phases: first contact, takeoff, and second contact. The minimal peak, average, and maximal peak values will be evaluated. To assess EMG activation, the tibialis anterior (TA), extensor digitorum longus (EDL), peroneus longus (PL), and medial gastrocnemius (MG) will be evaluated using the EMG analysis equipment Delsys (Trigno Avanti; Natick, USA), assessing the total average and ratios of contraction.

For skin preparation and electrode application and placement, the guidelines outlined in the Surface Electromyography for the Non-Invasive Assessment of Muscles (SENIAM) will be followed. (1) TA: The electrode is positioned on the front of the leg, over the muscle belly. The midpoint is approximately one-third of the distance between the tibia and the outer edge. (2) EDL: The electrode is also placed at the front of the leg, over the muscle belly. The midpoint of the muscle is one-third of the distance between the tibia and the outer edge. (3) PL: The electrode is situated in the lateral region of the leg, on the muscle belly. The midpoint is located at one-third of the distance between the tibia and the external border. (4) MG: The electrode is positioned on the back of the leg, over the muscle belly. The midpoint is approximately one-third of the distance between the bottom of the calf and the top of the heel.

To normalize the EMG signal, a normalization based on the activation during the maximum voluntary isometric contraction (MVIC) of each muscle will be performed. These evaluations will be conducted on the first day of the running protocol (Day 2). Participants will execute three isometric contractions against resistance for 5 seconds, with 15 seconds of rest between repetitions. For the TA, participants will be in a seated position and will perform dorsiflexion, adduction, and supination. For the EDL, participants, in a seated position, will execute pure eversion. The PL will be assessed with participants in a seated position, performing plantarflexion, abduction, and pronation. The MVIC assessment of the MG will involve participants lying prone with the knee extended, performing inversion.

**Jumping ability** will be assessed using the SLDJ test, and the characteristics of the jump will be analyzed with the MyJump 2 app. This test consists of a participant standing on one leg on a raised platform and then quickly dropping down and immediately jumping vertically with the same leg. The MyJump 2 app allows for the collection of several key variables, including:

- Jump Height: Measuring the vertical displacement from the initial jump.
- Flight Time: The duration the participant spends in the air during the jump.
- Contact Time: The time the participant's foot is in contact with the ground during the jump.
- Reactive Strength Index (RSI): Calculated as the ratio of jump height to contact time, providing insights into the efficiency of the jump.

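### Naming the Y-balance posterior reaches by right and left, when the stance limb may be either, would mix posteromedial with posterolateral reach if the labels become analysis variables

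*Protocol*

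**What the plan says.** The Lower limb stability paragraph of the Variables section tests one limb only: "The Y balance test will be used to analyze the stability of the dominant lower limb". Participants balance on that leg and reach with the other "along each of the three branches of the Y: anterior, posterior-right and posterior-left". The scoring rule is "Measurements will be taken from the tip of the foot in each direction, with three trials conducted to obtain an average". It gives a mean over trials and does not turn the two posterior branches into directions relative to the stance limb. No composite of the three reaches is defined.

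Which leg is dominant varies by person and is recorded only to describe the sample: "dominant limb (right or left), and history of ankle sprains will be collected as descriptive data". The Participants section places no condition on dominance.

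The Intervention protocol section tapes the same leg that is tested: "The bandaging will be consistently applied to the dominant leg by a physiotherapist". The Statistical analysis section plans a 3 x 2 repeated-measures ANOVA (condition by time) and adds "All variables will be analyzed individually, and multiple comparisons will account for using a Bonferroni correction". Side of dominance is not a factor in that model.

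**The concern.** Posterior-right and posterior-left are absolute sides. What matters for the taped ankle is the side relative to the stance leg. Standing on the right leg, a reach to the rear right is posterolateral and one to the rear left is posteromedial. Standing on the left leg, the two swap. A variable called posterior-right therefore holds one task for right-dominant runners and another for left-dominant runners.

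This could matter here because both techniques are asymmetric between the inner and outer ankle. Under Taping techniques, the longer KT strip goes up the outer side over the peroneus longus, and the figure-six strips of the rigid tape begin and end on the inner anchor. The protocol states no direction-specific hypothesis, but different effects on medial and lateral reach are plausible. That difference is what absolute-side labels blur.

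**Working it through.** The protocol gives no sample size, effect size or power for the Y balance test, so there is no planned figure to reproduce. The check is a mixture calculation.

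**Inputs**
- From the protocol: posterior branches named by absolute side; stance limb is the dominant one; dominance right or left; no eligibility limit on dominance; each variable analysed separately.
- Assumed: p, the share of left-dominant participants (5%, 10%, 20%; the protocol gives none).
- Assumed for illustration: a taping effect of 3 cm on posterolateral reach and 0 cm on posteromedial reach; a 5 cm difference in level between the two reaches.

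**Effect seen under each label.** Let eL and eM be the true effects on posterolateral and posteromedial reach.
- posterior-right: (1 − p)·eL + p·eM, an error of p·(eM − eL) as an estimate of eL
- posterior-left: (1 − p)·eM + p·eL, an error of p·(eL − eM) as an estimate of eM

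The two errors are equal and opposite. If eL = eM, both are zero. If not, the larger effect is reduced and the smaller one is raised. The expressions are linear, so they hold equally for a condition difference at one time and for the pre-to-post change compared between conditions.

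**Effect in one direction only (eL = 3 cm, eM = 0)**

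| p | Factor on the real effect (1 − p) | posterior-right | posterior-left (true value 0) |
|---|---|---|---|
| 5% | 0.95 | 2.85 cm | 0.15 cm |
| 10% | 0.90 | 2.70 cm | 0.30 cm |
| 20% | 0.80 | 2.40 cm | 0.60 cm |

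**Between-person spread.** A level gap g adds a variance of g²·p·(1 − p), that is, an SD term of g·√(p(1 − p)). With g = 5 cm this is 1.1, 1.5 and 2.0 cm at p = 5%, 10% and 20%. It combines in quadrature with the existing spread. With an assumed between-person SD of 8 cm and measurement SD of 3 cm, the total SD at p = 20% goes from √(64 + 9) = 8.54 to √(73 + 4) = 8.77 cm.

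**Within-person contrast.** Each runner keeps the same stance leg in all three sessions, so the level gap drops out of any condition contrast. A simulation of 200,000 participants at p = 20%, with the SDs and gap above, agrees:
- Equal effects of 2 cm: 1.99 cm under the posterior-right label against 2.00 cm for true posterolateral reach, with an SD of the contrast of 4.23 cm in both.
- Effects of 3 and 0 cm: 2.41 against 3.01 cm, with SDs of 4.40 and 4.23 cm.

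**After recoding.** With directions defined relative to the stance limb, both error terms and the added SD term are zero for every p.

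**The case against.** The strongest reply is that the protocol never says left- and right-dominant data will be pooled by side. The sentence naming the branches tells participants where to reach, and the Statistical analysis section does not list posterior-right or posterior-left as endpoints. Converting branch and dominance into medial and lateral reach is a derivation that a SAP could hold, and any SAP is not at hand. This stands in part: the pooling is an inference. But the side labels are the only definition the protocol gives of these measurements, its model has no dominance term, and dominance is marked as descriptive. Followed as written, the plan mixes the two reaches.

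The second reply is that the crossover protects the comparison. It does so for differences in level, and fully if taping acts equally in both directions. It does not do so when the effects differ.

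Two stronger readings are tempting and should be resisted. A reader might infer that mixing dilutes every direction-specific effect; the formulas show that it reduces the larger and raises the smaller. A reader might also take the shrinkage of the medial-versus-lateral difference in effects, which is (1 − 2p), or 0.90, 0.80 and 0.60 at the same p, as the loss. The protocol plans no such contrast. It tests each variable separately, where the loss in the one-direction case is (1 − p).

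**Conclusion.** The point holds as a defect in an outcome definition, of low consequence. It needs at least one left-dominant participant, and it needs the side labels to be used as analysis variables. Bias in the condition effect further requires that taping acts differently on medial and lateral reach. In that case, with an effect in one direction only and 5% to 20% left-dominant runners, that effect is understated by 5% to 20% of its value and the same amount appears falsely in the other direction.

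Descriptive means and the spread of the posterior reaches are distorted even if the effects are equal, provided the two reaches differ in level. That spread would also enter the one-way baseline ANOVA if it were run as though the conditions were independent groups. The documents do not support a claim that the taping comparison is biased in general, or that the trial's main conclusion is at risk. Anterior reach is untouched, and the primary outcome, SLDJ height, does not use these labels.

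**What to change.** In the Lower limb stability paragraph, define the three reaches as anterior, posteromedial and posterolateral relative to the stance (dominant) limb, and state that these are the variables analysed. For right-dominant participants, posterior-right becomes posterolateral and posterior-left becomes posteromedial. For left-dominant participants the assignment is reversed. Dominance is already collected, so this is one changed line in the protocol and one recode in the dataset. It needs no further measurements, visits or participants, and it can be applied to data already recorded by side.

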***Tape Bandage***

The ankle taping procedure will be executed utilizing a conventional 38 mm self-adhesive tape, initiating with the application of two anchor straps at a position approximately 10 cm proximal to the malleoli. This will be followed by the strategic placement of two additional straps extending from the medial edge of the anchor strap to the lateral side, with the foot maintained in a neutral position. Subsequently, "figure six" configurations will be crafted, commencing with a strip originating from the medial anchor, passing through the plantar aspect of the foot, and reattaching to the medial anchor. To finalize the taping ankle procedure, the practitioner meticulously will cover all terminal ends and any laxity with adhesive tape, ensuring a secure and uniform application.

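### The written EMG electrode sites contradict themselves (MG) or do not tell two muscles apart (TA, EDL), and the MG and EDL reference contractions cannot be relied on as those muscles' maxima

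*Protocol*

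**What the plan says.** The Protocol's Variables section (electromyographic activation) lists EMG of TA, EDL, PL and MG during the drop jump. There are three phases (first contact, takeoff, second contact) and three summaries (minimal peak, average, maximal peak), plus a total average and contraction ratios.

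For skin preparation and placement it states that "the guidelines outlined in the Surface Electromyography for the Non-Invasive Assessment of Muscles (SENIAM) will be followed". It then gives its own landmarks:

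- TA, front of the leg: "The midpoint is approximately one-third of the distance between the tibia and the outer edge".
- EDL, also front of the leg: "The midpoint of the muscle is one-third of the distance between the tibia and the outer edge".
- PL, lateral region of the leg: "The midpoint is located at one-third of the distance between the tibia and the external border".
- MG: "The electrode is positioned on the back of the leg, over the muscle belly", followed at once by "The midpoint is approximately one-third of the distance between the bottom of the calf and the top of the heel".

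The next paragraph normalises each muscle's signal to its MVIC, recorded on the first running day. TA is tested in dorsiflexion with adduction and supination, EDL in eversion alone, and PL in plantarflexion with abduction and pronation. For MG: "The MVIC assessment of the MG will involve participants lying prone with the knee extended, performing inversion".

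Under Intervention protocol, the three conditions are tested in three sessions a week apart. Under Sample size calculation, the primary outcome is drop-jump height.

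**The concern.** An EMG channel represents a muscle only if the electrode lies over that muscle. A normalised value is a percentage of maximum only if the reference task elicits that muscle's maximum. The written rules put both in doubt. An assessor who works from the landmark sentences cannot tell the TA site from the EDL site and is sent below the calf for MG. MG is then scaled to a task that does not include plantarflexion, and EDL to one that resembles the PL task.

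At stake is the interpretation of the EMG outcomes: which muscle changed, how strongly it was active, and how muscles compare with each other. No later analysis can repair a wrong site or a wrong reference task.

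**Working it through.** The Protocol gives no figure to reproduce here. The check sets the statements side by side and follows the divisor algebraically.

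**1. TA against EDL.** Both are on the front of the leg, over the belly, at one-third of the distance from tibia to outer edge. Neither has a height along the leg. Apart from the muscle's name, the only difference is that the TA fraction is approximate, so the landmarks do not separate the two channels. PL repeats the fraction and differs only in being lateral.

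**2. MG.** Let L be the distance from the bottom of the calf to the top of the heel. The Protocol does not say from which end the third is measured, so the site is L/3 or 2L/3 below the bottom of the calf. Either way it is below the calf, whereas the preceding sentence puts it over the belly. Both cannot hold on an ordinary reading of the words.

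**3. Reference tasks.** Plantarflexion appears only in the PL task. That the gastrocnemius is mainly a plantarflexor, and EDL a toe extensor and dorsiflexor, is general anatomy and not a statement of the Protocol. On that basis inversion and eversion are not the main actions of MG and EDL.

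**4. What a wrong divisor does.** For participant i, muscle m, condition c and time t:

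%MVIC(i,m,c,t) = 100 × E(i,m,c,t) / D(i,m)

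E is the recorded activity and D the true maximum. D has no index c or t because one MVIC occasion is stated. Suppose the task elicits only k(i,m) × D(i,m), with k below 1. Then:

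- Level: %MVIC is multiplied by 1/k(i,m), so it is overstated.
- Post/pre or tape/control ratio within one muscle: k cancels, so there is no change.
- Absolute difference within one muscle, which is what the planned repeated-measures ANOVA compares if applied to %MVIC: multiplied by 1/k(i,m). A k common to all participants leaves the F statistic unchanged. A k that varies between participants weights them unequally and adds noise.
- Ratio of muscle 1 to muscle 2: multiplied by k(i,2)/k(i,1), which does not cancel unless the two k are equal.

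**5. Limit of the cancellation.** It assumes the same site at each session. With a site-dependent gain g(i,m,s) at session s, a between-session ratio carries the factor g(i,m,s)/g(i,m,s′). Each session is one condition, so this enters the comparison of conditions. Landmarks without a height make such shifts more likely. With randomised order and placement error unrelated to condition, the result is noise rather than a systematic shift.

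**6. Reach.**

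- Per-muscle values at each assessment: 4 muscles × 3 phases × 3 summaries = 36, or 9 per muscle, before total averages and ratios.
- Site wording in question (TA, EDL, MG): 3 × 9 = 27.
- Reference task in question (EDL, MG): 2 × 9 = 18.
- If the contraction ratios are between muscles, four muscles form 4 × 3 / 2 = 6 pairs. Only TA with PL avoids both EDL and MG, so 5 of 6 involve a doubtful divisor.

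**The case against.** The strongest reply is that the same paragraph invokes a placement guideline and puts every electrode over or on the muscle belly. An experienced operator who follows those statements would record the named muscles. This stands. The text contradicts itself; it does not prescribe only wrong sites. A protocol that gives a general rule and landmarks that do not fit it still needs correcting, because the reader cannot know which was followed.

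A second reply is that one MVIC per muscle cancels in proportional comparisons, and that every participant undergoes all three conditions. This also stands for the divisor, within the limit in step 5. It does not rescue absolute levels or between-muscle ratios. The Protocol does not say that its contraction ratios are between muscles, so that part is conditional.

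Four stronger readings are tempting, and the documents do not support them:

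- A reader might infer that TA and EDL would be one signal counted twice. With no height given, the site is under-specified rather than fixed at a single shared point.
- A reader might put a size on the overstatement of MG activity. The Protocol gives nothing on how much of the MG maximum inversion elicits.
- A reader might infer that the MG electrode would sit beside the tape, since the Tape Bandage section places "two anchor straps at a position approximately 10 cm proximal to the malleoli". The MG landmark is a fraction of an unstated length from an unstated end, so overlap cannot be shown.
- A reader might say the reference tasks breach the cited guideline. The sentence citing it covers skin preparation and electrode application and placement, not the MVIC tasks, and the guideline's content is not in the documents.

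**Conclusion.** The point holds for the EMG outcomes. The MG landmark contradicts the sentence before it, the TA and EDL landmarks are not distinguished, and the MG and EDL reference tasks cannot be relied on to give those muscles' maxima. Followed literally, the rules leave per-muscle values, %MVIC levels and any between-muscle ratios unreliable as measures of the named muscles. The counts in step 6 show how many outcomes are exposed, not how many would be wrong.

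The site finding rests on the Protocol's own words. The reference-task finding also rests on general anatomy. No numerical bias can be given. Drop-jump height, the primary outcome, is measured by a phone app and is unaffected. The matter should be settled before the first EMG session, but it does not threaten the main comparison.

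**What to change.** - Replace the four landmark sentences with a distinct on-belly site for each muscle, stating height along the leg and side. Follow the placement guideline already cited where it covers the muscle.
- Record each participant's site as measured distances, so that the same sites are used at all three weekly sessions. A skin mark alone may not last between sessions.
- Use a reference contraction that matches each muscle's main action: resisted plantarflexion for MG, and resisted toe extension or dorsiflexion for EDL.
- If TA and EDL cannot be separated at the surface, report them as one dorsiflexor channel.
- State whether the contraction ratios are between muscles.

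The cost is Protocol wording and a few minutes of measurement per participant. No visit or equipment is added.
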